## Abstract

**Background:**

In patients with severe polycystic liver disease (PLD), there is a need for new treatments. Estrogens and possibly other female sex hormones stimulate growth in PLD. In some patients, liver volume decreases after menopause. Female sex hormones could therefore be a target for therapy. The AGAINST-PLD study will examine the efficacy of the GnRH agonist leuprorelin, which blocks the production of estrogen and other sex hormones, to reduce liver growth in PLD.

**Methods:**

The AGAINST-PLD study is an investigator-driven, multicenter, randomized controlled trial. Institutional review board (IRB) approval was received at the University Medical Center of Groningen and will be collected in other sites before opening these sites. Thirty-six female, pre-menopausal patients, with a very large liver volume for age (upper 10% of the PLD population) and ongoing liver growth despite current treatment options will be randomized to direct start of leuprorelin or to 18 months standard of care and delayed start of leuprorelin. Leuprorelin is given as 3.75 mg subcutaneously (s.c.) monthly for the first 3 months followed by 3-monthly depots of 11.25 mg s.c. The trial duration is 36 months. MRI scans to measure liver volume will be performed at screening, 6 months, 18 months, 24 months and 36 months. In addition, blood will be drawn, DEXA-scans will be performed and questionnaires will be collected. This design enables comparison between patients on study treatment and standard of care (first 18 months) and within patients before and during treatment (whole trial). Main outcome is annualized liver growth rate compared between standard of care and study treatment. Secondary outcomes are PLD disease severity, change in liver growth within individuals and (serious) adverse events. The study is designed as a prospective open-label study with blinded endpoint assessment (PROBE).

**Discussion:**

In this trial, we combined the expertise of hepatologist, nephrologists and gynecologists to study the effect of leuprorelin on liver growth in PLD. In this way, we hope to stop liver growth, reduce symptoms and reduce the need for liver transplantation in severe PLD.

*Trial registration* Eudra CT number 2020-005949-16, registered at 15 Dec 2020. https://www.clinicaltrialsregister.eu/ctr-search/search?query=2020-005949-16.

## Background

Polycystic liver disease (PLD) is a rare disease, characterized by the presence of > 10 liver cysts [1]. Autosomal Dominant Polycystic Liver Disease (ADPLD) leads to PLD only and is caused by a mutation in *PRKCSH*, *SEC63*, *LRP5*, *ALG8* or *SEC61B* [1]. Autosomal Dominant Polycystic Kidney Disease (ADPKD) can cause PLD but also leads to kidney cysts and renal function decline [1–3] and is most frequently caused by a mutation in the *PKD1* or *PKD2* gene [4, 5]. The *PKD1* and *PKD2* genes encode for ciliary proteins polycystin 1 and polycystin 2, respectively, while the mutations in ADPLD affect maturation and trafficking of polycystin 1 [3, 4]. The prevalence of ADPLD is < 1:10.000 [6], the point prevalence of clinically relevant ADPKD approximately 1:2500 [7], but not all ADPKD patients suffer from PLD [8].

PLD patients have a normal liver function in general, but large liver volumes can lead to serious physical and psychosocial complaints [1, 9]. The large liver can compress the stomach and bowels, leading to early satiety, decreased food intake, weight loss, sarcopenia and constipation [1, 9]. The increased intra-abdominal volume can lead to pain, and diaphragmatic, umbilical and inguinal herniation [1] and compression of vascular structures can lead to ascites, portal vein thrombosis or hepato-venous outflow obstruction [10]. The large, protruding abdomen may cause psychological problems, because of distorted body image and confronting questions about possible pregnancy [1, 9]. This can result in decreased quality of life, and sometimes liver transplantation is the only and last resort treatment option [11, 12].

### An unmet need for new treatments

Dependent on the cyst distribution, different treatments are possible. In case of several dominant liver cysts, aspiration or fenestration is used [1, 9]. If liver cysts are clustered in a few liver segments, a hemihepatectomy can be performed [1]. In case of numerous liver cysts in all segments, surgical interventions are not possible and the mainstay of treatment is to halt natural growth [1, 9]. The only treatment now available to halt growth of liver cysts are somatostatin analogues, but in about 40% of patients treated with these drugs liver growth continues (Fig. 1) [13]. In these patients, the only treatment option that remains is a liver transplantation [1, 9, 12]. In the last 15 years, 1293 liver transplantations have been performed in Europe to treat PLD [12]. Therefore, there is a continuing unmet need for new therapies in PLD.

**Fig. 1 Fig1:**
[figure not shown]
MRI scan (coronal T2-weighted image) of a patient with severe PLD and ongoing liver growth despite somatostatin analogue use, that would be eligible for the AGAINST-PLD study

### Female hormones in PLD

Female sex is the most important risk factor for PLD [14]. About 90% of patients is female [14, 15]. Several factors indicate that female sex hormones stimulate cyst growth. First, estrogen supplementation leads to enhanced liver growth [16, 17] and after menopause, when estrogen and progesterone levels fall, liver volumes sometimes decrease spontaneously [18]. Second, estrogen receptors are present on hepatic cyst epithelium and in vitro, liver growth increases after estrogen supplementation and decreases after administration of estrogen blockers [19–22]. In a recent review paper, we explained in detail how the female sex hormones estrogen and progesterone may affect liver growth and how these hormones could be a target for therapies [22]. While there is a lot of evidence that estrogen affects liver cyst growth, it is difficult to disentangle the contributions of the individual sex hormones, like estrogen and progesterone, on PLD. Oral contraceptives mostly contain estrogen as well as progesterone and menopause also affects both hormones. Therefore, it is unclear whether other sex hormones than estrogen, such as progesterone, affect liver growth.

An ideal therapy should block all estrogen receptors and should block also other sex hormones, such as progesterone. For estrogen only, three different estrogen receptors [22] are present on hepatic cyst epithelium: ER-α, ER-β and the G-coupled protein estrogen receptor 1 (GPER-1) [19–23]. Selective estrogen receptor modulators (SERM), such as tamoxifen, act as agonist or antagonist on ER-α and ER-β, dependent on the surrounding tissue [24, 25]. Currently it is not possible to predict the effects of SERMs in PLD. Besides, the effect on the GPER-1 receptor (inhibition or stimulation) is unclear. Therefore, in this trial, we aim to reduce liver growth in patients suffering from severe PLD using the Gonadotropin Releasing Hormone (GnRH) agonist leuprorelin. This drug leads to cessation of the production of estrogen as well as progesterone and other female hormones, aiming to stop liver growth, but with medically induced menopause as logical adverse event [26].

### Objectives

The main trial objective is:To determine whether lowering estrogen and progesterone levels with the GnRH agonist leuprorelin decreases liver growth rates (%/y) in pre-menopausal women with severe PLD when compared to similar women not receiving this treatment.
Secondary objectives are:To assess the effect of leuprorelin on PLD disease severity, measured with the PLD-Questionnaire (PLD-Q)To assess the change in liver growth within individuals before and during leuprorelin treatmentTo assess the tolerability and incidence of (serious) adverse events.
Exploratory outcomes are:To assess estrogen and progesterone levelsTo assess differences in short term and long term effects of treatmentIn case of ADPKD, to assess the effect on kidney growth and renal function decline.

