## Methods and design

### Study design

The AGAINST-PLD study (A GnRH Agonist IN premenopausal women Study to Treat Polycystic Liver Disease) is a 3-year lasting, investigator driven, phase 2b randomized controlled trial. Participants will be randomized between direct start or delayed start (18 months later) of leuprorelin treatment (Figs. 2, 3). Patients randomized to delayed start will receive standard of care in the first 18 months of the trial. Therefore, in the first 18 months of the trial, we can distinguish between the effect of treatment and the natural course of disease by comparing both treatment arms. Using data obtained during the second 18 months of the trial, when all patients are subjected to active treatment, we can compare liver growth rates within individuals before start of treatment and during treatment and obtain more information about safety and tolerability.

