### Patient selection

Detailed inclusion criteria are given in Table 1, of which the most important are:Female patients, pre-menopausalAnti Mullerian Hormone (AMH) level > 0.3 (a lower level indicates upcoming menopause)Age 18–45 years (inclusive)PLD with a very large liver for age, based on the upper 10% of volumes in our PLD registry (n = 1600) [27].One historical MRI or CT scan, performed 1–5 years before baseline, available to calculate liver growth before start of the studyOngoing liver growth, confirmed using a historical scan (a) obtained in routine clinical care and the scan at screening (b) with the liver volume in ml from scan b–a > 0.Use of a somatostatin analogue (only proven effective therapy currently available) or reason not to use such drug (e.g. not tolerated, ineffective, not available)

**Table 1 Tab1:** Overview of in- and exclusion criteria for the AGAINST-PLD study

Inclusion criteria	
Female	
Diagnosis of PLD (presence of > 10 cysts)	
Age 18–45 (inclusive) years	
Very large liver for age:	
18–30 y hTLV > 2.0 L/m	
30–35 y hTLV > 2.2 L/m	
25–40 y hTLV > 2.5 L/m	
40–45 y hTLV > 3.0 L/m	
1 historical MRI or CT scan of the liver available, made 5-1 y before baseline	
Ongoing liver growth, confirmed using the historical scan and MRI scan at screening	
Use of somatostatin analogues OR a reason not to use them (e.g. tried in de past but stopped because of side effects, not effective, no acces, patient does not want to)	
Voluntary written informed consent	

Exclusion criteria	
Post menopausal status or (vasomotor) symptoms indicating upcoming menopause	
AMH < 0.03 ng/ml at screening	
Active desire to have children, pregnancy or breast-feeding	
Contra-indications for leuprorelin, such as cardiovascular disease or osteoporosis	
Liver transplantation expected within 1.5 years	
Use of oral estrogen or progesterone containing medication	
Contra-indications for MRI	
Chronic use of immunosupressive agents	
Severe hypertension (systolic pressure ≥ 160 and/or diastolic pressure ≥ 100 mmHg)	
Clinically significant uncontrolled medical condition that, in the opinion of the investigator, would put the safety of the patient at risk though participation, or which would affect efficacy or safety analysis, such as, but not limited to, recurrent cholangitis, recurrent ascites, hepato-venous outflow obstruction, (history of) depression	
Participation in other interventional studies at the same time	

Exclusion criteria related to the historical MRI/CT scan	

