### Randomization

Participants will be randomized 1:1 between direct and delayed start (after 18 months) of treatment using an online Interactive Response System (IXRS) tool, stratified for somatostatin analogue use (yes/no) and age (< 40 and ≥ 40 years).

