#### Secondary outcomes

Change in PLD disease severity, assessed by the validated PLD-Q questionnaire, calculated over the first 18 months of the trial and compared between the direct start group (on treatment) and delayed start group (on standard of care).Liver growth rates within individuals compared before treatment and during treatment. In the direct start group, historical growth rates (Fig. 3a, b) will be compared with growth rate during 18 months of treatment (b–e) and in the delayed start group, growth rates during the first 18 months of the trial (untreated, b–c) will be compared with the last 18 months of the trial (treated, c–d).The incidence of (serious) adverse events, compared between the direct and delayed start group in the first 18 months of treatment.

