**Fig. 4 Fig4:**
[figure not shown]
Visit schedule. S = screening, BL = baseline, V = visit, P = phone call. Screening procedures can take place in one visit or with MRI and DEXA apart, as preferred by site and patient. Patients are randomized to direct start (at BL) or delayed start (at V5). A phone cal (P) takes place one month after first leuprorelin injection. More extensive visits with MRI, questionnares and extensive lab take place at BL, 6, 18, 24 and 36 months. Extensive lab consists also of biobanking (samples stored at − 80 °C and shipping to core laboratory for measurement of female sex hormones in one run) and in case of ADPKD, 24 h urine collection. Between visits, site personnel will remind patients to administer the leuprorelin injections by phone or email

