### Laboratory measurements

For a detailed overview of collected samples, see Fig. 4. At all visits, a limited set of laboratory measurements will be performed. At baseline and the visits at month 6, 18, 24 and 36, more extensive laboratory measurements, biobanking and in ADPKD patients, 24-h urine samples will be collected. Except form biobanking samples, laboratory samples will be analyzed locally. Biobanking samples will be stored at − 80 °C and shipped to the core laboratory at the end of the trial to measure estrogen, progesterone, AMH, FSH and LH in one run, to minimize interlaboratory and interassay variation.

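### For ADPKD renal function the plan lists only a before-versus-on-treatment contrast; the randomised 18-month comparison given for kidney growth should be listed too (exploratory outcome, low severity)

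*Protocol article*

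**What the plan says.** All places are in the protocol article.

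- **Objectives.** In ADPKD, an exploratory aim is "to assess the effect on kidney growth and renal function decline".
- **Exploratory outcomes.** Kidney growth has two comparisons: direct versus delayed start over the first 18 months, and within individuals before versus on treatment. Renal function has one line, which contrasts decline before treatment with decline on it. No between-arm comparison is named.
- **Statistical analysis.** No renal-function analysis is described.
- **Study design.** Of the first 18 months, the article says "we can distinguish between the effect of treatment and the natural course of disease by comparing both treatment arms". The within-individual use of the second 18 months is presented as an addition, for liver growth.
- **Randomization and Fig. 4 legend.** "Participants will be randomized 1:1 between direct and delayed start (after 18 months) of treatment"; direct starters begin at baseline, delayed starters at the month-18 visit.
- **Secondary outcomes.** For liver growth, the missing untreated period of direct starters is filled from earlier scans: "In the direct start group, historical growth rates (Fig. 3a, b) will be compared with growth rate during 18 months of treatment".
- **Patient selection, Table 1.** The historical item required at entry is "1 historical MRI or CT scan of the liver available, made 5-1 y before baseline". No historical creatinine or eGFR is mentioned.
- **Laboratory measurements.** "At all visits, a limited set of laboratory measurements will be performed". At baseline and months 6, 18, 24 and 36, "more extensive laboratory measurements, biobanking and in ADPKD patients, 24-h urine samples will be collected". No difference by arm is stated.

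**The concern.** The aim is causal: the effect of leuprorelin on renal function decline. The listed contrast is uncontrolled in both arms, for different reasons.

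In delayed starters, treatment and time coincide completely. If decline naturally steepens or flattens over three years, the change would be read as harm or benefit of the drug. In direct starters, treatment begins at baseline, so the trial itself provides no untreated slope. An earlier slope would have to come from values whose source, timing and standardisation the article does not state.

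The design already contains a better comparison, which the article uses for kidney growth in the same list. At stake is the reading of one exploratory outcome in a subgroup. If the between-arm comparison is added only once results are known, it will look like a post hoc choice.

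**Working it through.** **Plan's own figure.** None is given for renal function, so there is nothing to reproduce. The planned total of 36, randomised 1:1, caps the subgroup at 18 per arm.

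**Step 1. What each contrast estimates.** Let the mean untreated slope be s in months 0–18 and s + g in months 18–36, and let the drug add d.

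- Delayed starters, before versus on treatment: (s + g + d) − s = d + g.
- Direct versus delayed start, months 0–18: (s + d) − s = d.
- Direct starters, before versus on treatment: not estimable from trial data.

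The bias of the first contrast is g, whatever the sample size. A simulation with d = 0 and g = 0, −0.5 and −1.0 mL/min/y, with 14 patients per arm, gave within-patient estimates of 0.00, −0.50 and −1.00. The randomised contrast stayed within 0.01 of zero.

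**Step 2. Precision.** The article gives no ADPKD share, slope or SD. Everything below is assumed, with m ADPKD patients per arm and no dropout.

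*Noisier inputs:* m = 9, residual eGFR SD σ = 3, between-patient slope SD τ = 2, values at 0, 6 and 18 months and then at 18, 24 and 36 months.

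- Times in years are 0, 0.5 and 1.5, so Sxx = 1.167. The second period has the same Sxx.
- Error variance of one slope: 9/1.167 = 7.71.
- Between arms: SE = √[2(7.71 + 4)/9] = 1.61.
- Within delayed starters, τ cancels, but both slopes share the month-18 value, with covariance 9 × 0.714 × (−0.571) = −3.67. SE = √[(7.71 + 7.71 + 7.35)/9] = 1.59.
- With σ = 5 and τ = 3: 2.60 between arms, 2.65 within.

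*Quieter inputs:* slope SD 2 between patients and SD 1 within each period.

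- Between arms: SE = √[2(4 + 1)/m]. Within: SE = √[2(1)/m].
- The ratio is √5 = 2.24 at any m.

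| m per arm | SE randomised | SE within-patient | Slope difference with 80% power, in SD units |
|---|---|---|---|
| 9 | 1.05 | 0.47 | 1.32 |
| 14 | 0.84 | 0.38 | 1.06 |
| 18 | 0.75 | 0.33 | 0.93 |

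The last column is (1.96 + 0.84) × √(2/m). With m = 9 and slope SD √5 = 2.24, the detectable difference is 1.32 × 2.24 = 2.95 mL/min/y. That is about as large as the assumed mean decline of 3.

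**Step 3. What the bias does to a nominal 5% test.** Take g = 1, d = 0, m = 9 and a paired t-test with 8 df and non-centrality 1/SE. For the noisier inputs (SE 1.59 to 2.65) it rejects in about 9% to 6% of trials. For the quieter inputs (SE 0.47) it rejects in about 46%. The more precise the within-patient contrast, the more often a time trend passes for a drug effect.

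**Step 4. Total error, quieter inputs, m = 14.** Root-mean-square error within patients is √(0.38² + 0.5²) = 0.63 at g = 0.5 and √(0.38² + 1²) = 1.07 at g = 1. The randomised contrast has 0.84 in both cases. They break even at g = √(0.84² − 0.38²) ≈ 0.75 mL/min/y.

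**The case against.** The strongest reply is that one short line at the end of an exploratory list is a label, not an analysis. It names no measure, test, window or arm, and a condensed article may leave those to the full protocol or SAP. It also lacks the within-individual qualifier of the kidney-growth line, so a model of treated versus untreated time across both arms would fit it. That is a possible reading. But the article names a contrast, and names it differently from the sister outcome a few words earlier. That is more than omitted detail.

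A reader might also infer that direct starters can have no earlier renal data. The text does not support that. Historical scans come from routine care, and silence about creatinine in the eligibility table does not exclude routine renal values. What stands is that no source is named.

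Nor can it be claimed that the randomised comparison costs little precision. Step 2 shows anything from equal to more than double the standard error, and at a small time trend the within-patient contrast has the lower total error. This supports keeping that contrast, but not as the only answer to a question about effect.

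Finally, the text does not say which laboratory set contains creatinine; the detail is in a figure not shown. The main calculation therefore uses only the extensive-laboratory visits.

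**Conclusion.** The point holds, at low severity. As listed, the renal-function outcome cannot separate drug from time in delayed starters and has no stated comparator in direct starters. The between-arm comparison that the article itself presents as separating treatment from natural course is listed for kidney growth but not here.

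The bias equals the natural change in slope. Whether that change is trivial or material cannot be judged from the article, since all renal slopes, SDs and the ADPKD share above are assumptions. The randomised comparison removes this bias but will be imprecise in a small subgroup.

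It would be wrong to infer that the trial's conclusions are at risk. The outcome is exploratory, kidney growth is not affected, and the primary liver-growth result does not depend on it.

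**What to change.** Add one line under Exploratory outcomes: renal function decline from baseline to month 18, compared between the direct and delayed start groups and adjusted for baseline renal function. Name it as the main renal-function comparison. The adjustment is useful because randomisation is stratified by somatostatin analogue use and age, not by disease type, so a small ADPKD subgroup may be unbalanced at baseline.

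Keep the before-versus-on-treatment contrast as supportive. Either restrict it to delayed starters, or state where the pre-trial renal values of direct starters come from. Report both with confidence intervals.

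The cost is one outcome line and one model, with no new visits, samples or patients. The downside is an interval that may be about twice as wide as the within-patient one, with low power. The change should be made before the data are analysed.

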## Methods and design

### Study design

The AGAINST-PLD study (A GnRH Agonist IN premenopausal women Study to Treat Polycystic Liver Disease) is a 3-year lasting, investigator driven, phase 2b randomized controlled trial. Participants will be randomized between direct start or delayed start (18 months later) of leuprorelin treatment (Figs. 2, 3). Patients randomized to delayed start will receive standard of care in the first 18 months of the trial. Therefore, in the first 18 months of the trial, we can distinguish between the effect of treatment and the natural course of disease by comparing both treatment arms. Using data obtained during the second 18 months of the trial, when all patients are subjected to active treatment, we can compare liver growth rates within individuals before start of treatment and during treatment and obtain more information about safety and tolerability.

**Fig. 2 Fig2:**
[figure not shown]
Infographic about the AGAINST-PLD study

**Fig. 3 Fig3:**
[figure not shown]
Study design of the AGAINST-PLD study. Patients are randomized between direct and delayed start (after 18 months) of treatment. **a** Historical scan, **b** baseline scan, **a**, **b** historical growth. Primairy outcome, comparison between growth on treatment and without treatment in the first 18 months is **b**, **c** versus **b**, **e**. Secondary outcome, growth within individuals before and during treatment is **b**, **c** versus **c**, **d** and **a**, **b** versus **b**, **e**

